### Further information on the study products

#### Hyaluronic acid

One of the non-operative options used for reducing pain and maintaining hip mobility in patients with hip OA is viscosupplementation. Viscosupplementation is the administration of HA preparations into the affected joint to supplement the viscoelasticity of the diseased synovial fluid.

The underlying mechanisms of action of HA in osteoarthritic joints are not completely understood. There is increasing evidence to indicate that clinical efficacy is mediated through several pathways: anti-inflammatory effects, anti-nociceptive effects, normalization of endogenous HA synthesis and chondroprotection [23].

It takes less than a day to clear the injected HA from the osteoarthritic joint [24]. To increase the average intra-articular half-life, TRB Chemedica produced Ostenil Plus which will be used in our study. Ostenil Plus has a higher a concentration of hyaluronic acid (40 mg/2 ml) which is twice as much as previously used in the product Ostenil. In addition Ostenil Plus contains 10 mg Mannitol, an antioxidant which protects hyaluronic acid molecules against free radicals and inhibits the degradation of HA [25]. Ostenil Plus is a low molecular weight hyaluronic acid (LMW HA) (1.6 million Dalton).

One meta-analysis showed no important evidence for a clinically relevant benefit of a high molecular weight hyaluronic acid (HMW HA) compared with LMW HA in patients with OA of the knee [26]. The authors concluded that given the lack of a superior effectiveness of HMW HA over LMW HA and the increased risk of local adverse events associated with the first, it is better to use intra-articular LMW HA in patients with OA of the knee in clinical research or practice.

There is one study comparing low and high molecular weight HA following intra-articular administration in hip OA patients [27]. The authors concluded that both treatments produced a significant reduction in OA symptoms but there was no statistically significant difference between the two groups. This study had a small patient population (32 hips LMW HA and 24 hips HMW HA) and they did not use a power calculation to prove that they included enough patients.

Viscosupplementation, performed with the use of fluoroscopy or ultrasound guidance, is an effective treatment of hip OA and can be an alternative method to other conservative treatments or total hip arthroplasty [14,28,29].

Intra-articular injection of HA or its derivates into the hip joint is safe and well tolerated. However, local adverse reactions (hot, painful, swollen joint) were reported, typically occurring 24-72 hours, and mostly after injection of HMW HA (Hylan) in the knee [30-33]. Ten to thirty per cent of hip OA patients treated with intra-articular injections of HA reported adverse effects, which is slightly higher than in OA of the knee [13]. Some patients experienced transient hip pain after the infiltration but all of them fully recovered in the following days without any treatment or with the use of NSAIDs. Although a single case of septic arthritis was reported after multiple intra-articular injections [13], gout, pseudogout and chondrocalcinosis have not been reported after hip infiltrations with HA.

#### Corticosteroids

Due to their anti-inflammatory effects, CS have been used in the treatment of knee OA for many years. Intra-articular infiltrations of CS in the hip can also reduce pain, stiffness and disability. Clinical experience has shown that CS are very useful for the treatment of exacerbations of OA, but they do not influence the underlying process of OA. CS are useful for acute periods of pain in hip OA but this effect only lasts for some months [7,8,34]. A significant pain reduction at rest and during activity was seen at 3 and 12 weeks follow-up. The range of joint motion increased significantly for all directions and functionality improved significantly after the injection of CS [35,36].

It is well known that intra-articular injections of CS have some side effects, particularly after repeated injections. These include thinning of the cartilage, a higher risk of infection and weakening of the ligaments of the injected joint.

Two doses of CS (40 mg and 80 mg) were used in one study [34]. At 6 weeks, the benefits of the 40 mg and 80 mg doses in improving pain and stiffness of the hip were similar. However hip function did not improve with the 40 mg dose but only with the 80 mg dose [34].

In this study we will use Depomedrol 80 mg/2 ml.

#### Bupivacaine

Bupivacaine is a member of the amide group in the local anesthetic family and has a molecular weight of 342.9 g/mol. Because chondrocyte apoptosis has been implicated in the development of OA [37], it is important to determine whether bupivacaine has cytotoxic effects on articular chondrocytes. Chu et al (2006) showed that in vitro exposure of bovine articular chondrocytes to 0.5% bupivacaine was cytotoxic and that in cartilage with an intact surface bupivacaine caused less cell death [38]. The authors concluded that an intact articular surface may provide a partial barrier to cytoxicity due to bupivacaine.

A rabbit shoulder model showed no permanent impairment of cartilage function 3 months after intra-articular infusion of bupivacaine [39]. Cartilage metabolism was higher than before indicating a reparative ability to recover from the damage caused by bupivacaine. No difference in clinical outcome was seen between 0.5% bupivacaine and placebo [40,41]. After total knee arthroplasty, the use of bupivacaine reduced pain and the need for narcotics during the first 24 hours [41]. Microscopic evaluation of human articular chondrocytes showed more than 95% cell death after exposure to 0.5% bupivacaine for 30 minutes [38]. Chondrocytes exposed to 0.25% bupivacaine showed a time-dependent reduction in viability, with longer exposure resulting in more cellular death that continued even after removal of bupivacaine. Finally, exposure to 0.125% bupivacaine for up to 60 minutes did not influence the viability of chondrocytes in comparison to a saline solution. Thus, human chondrocytes may tolerate bupivacaine 0.125%. Large human joints show a peak absorption of bupivacaine within the first hour [42,43]. The combination of systemic absorption and either lavage fluid or effusion is sufficient to dilute the injected bupivacaine to a concentration of less than 0.125%, which reduces the potential for chondrotoxity [44]. In this study we will use Marcaine (0.125%/2 ml bupivacaine).

### Description of methodology

This is a randomized, masked-observer, controlled trial with three-armed parallel-group design. Patients meeting the inclusion/exclusion criteria will be randomized to one of the following treatment groups:

1. Infiltration of the hip joint with Hyaluronic Acid.

2. Infiltration of the hip joint with Corticosteroids.

3. Infiltration of the hip joint with 0.125% Bupivacaine.

A block randomization scheme, with a block size equal to 8, will be used for the randomization to avoid at random imbalances in group size. No stratification variables are considered in the randomization.

Efficacy parameters will be assessed at baseline and at the planned follow-up visits at 6 weeks, 3 months and 6 months after the injection.

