**Exclusion criteria:**

1. Kellgren and Lawrence grade 4,
2. an intra-articular hip injection (with any corticosteroid, hyaluronic acid preparation or other) within the previous three months,
3. rapid destructive hip OA.
4. a history of crystalline arthropathy or inflammatory arthritis, neuropathic arthropathy,
5. current other problem in the affected extremity,
6. allergy or hypersensitivity to any of the study medications or to contrast solutions.

Eligible patients that accept to participate will be asked to sign the informed consent form and will be assigned an inclusion number. Approximately 1 month later they will have their treatment (= infiltration).

At day 0 [the day of the infiltration (table 2)] demographic data including age, height, weight, body-mass index (BMI), target hip joint, and the use of nonsteroidal anti-inflammatory drugs will be recorded. The type of treatment the patient will receive will be checked. A nurse working at our day hospital will check the inclusion number and from the internet site http://www.randomizer.org she will, on the day of infiltration, obtain a randomized number ranging from 1 to 3 which corresponds to the treatment injection to be given.

**Table 2 T2:** Flowchart

Day ??	Day of inclusion:	Demographic data, clinical history, concomitant medication, informed consent, inclusion/exclusion criteria.
Day 0	Day of infiltration:	Pain (VAS), HOOS and HHS-score, randomization and infiltration.
Day 1-14	Diary:	Daily VAS and use of pain killers per day.
Week 6	Second consultation:	VAS, HOOS and HHS-score.
Week 12	Third consultation:	VAS, HOOS and HHS-score.
Week 26	Fourth consultation:	VAS, HOOS and HHS-score, end follow-up.

Approximately 315 patients will be included in the study. (see: Planned statistical analysis and sample size calculation).

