A sample size calculation was performed to have at least 80% power to detect in both groups compared with placebo, a clinically meaningful difference in change (baseline-6 months) of 10 mm in VAS and 10 points in HSS. The SD of HSS and VAS is assumed to be equal to 16 and 20 respectively. Estimates are obtained from Frihagen et al. [46] and Qvistgaard [15]. Assuming a moderate correlation of 0.5 between the measurement at baseline and after 6 months, a total of 285 patients are needed, i.e., 95 subjects in each group. With this sample size, 80%power is achieved for VAS and 96.2% for HHS. The number of included subjects will be increased by 10% to compensate for the loss of power due to patients with missing observations (therefore, 105 patients per group will be recruited). Interim analyses are planned after 1/3 and 2/3 of the patients included reach the end of the follow-up period to allow for an early stopping of the study (or accrual of patients in a specific treatment group) due to rejection of the null hypothesis. Using the O'Brien-Fleming method (O'Brien and Fleming 1979) results in respectively |4.495|, |3.178| and |2.595| as critical values for the Z-statistic at the three analysis time points. Otherwise stated, p-values are declared significant if they reach p < 0.000007, p < 0.00148 and p < 0.0095 at the first interim analysis, the second interim analysis and at the final analysis, respectively. (Note that the 'price to pay' for performing the interim analysis is a slightly more conservative alpha-level at the final analysis, i.e. alpha = 0.0095 instead of alpha = 0.01)

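### The stated block size of 8 does not fit a three-arm trial planned with equal groups, and the day-0 allocation procedure describes no blocks at all

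*Protocol article*

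**What the plan says.** In the protocol article, Description of methodology calls the study a "controlled trial with three-armed parallel-group design" and fixes the allocation method, a block scheme "with a block size equal to 8, will be used for the randomization to avoid at random imbalances in group size". It adds that "No stratification variables are considered in the randomization", so a single block sequence serves the whole trial.

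Planned Statistical Analysis & Sample size calculation assumes equal arms: "a total of 285 patients are needed, i.e., 95 subjects in each group", raised by 10% for missing observations so that "105 patients per group will be recruited". The paragraphs after the exclusion criteria give the matching total: "Approximately 315 patients will be included in the study".

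Those same paragraphs describe allocation in practice. On the day of the infiltration, a day-hospital nurse checks the inclusion number and takes a random number between 1 and 3 from a public website, and that number decides the product injected. Blocks are not mentioned there.

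**The concern.** Two things do not fit together. First, a permuted block gives equal allocation only if its size is a multiple of the number of arms, and 8 is not a multiple of 3. A statistician preparing the list must either depart from the stated size or invent a rule for the arm that gets two places instead of three. The article chose to state this parameter, so this is a value that does not work for the design, not a detail left to another document.

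Second, the article describes two different procedures. A separate 1-to-3 draw for each patient is not a block scheme, and it offers no protection against the chance imbalance that the blocks are meant to limit.

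What is at stake is mainly whether the randomisation is reproducible and correctly reported. Power is a secondary matter. VAS is the outcome that fixes the sample size, at 80% with no reserve, so a clear imbalance would show there first.

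**Working it through.** **Inputs** (Description of methodology; Planned Statistical Analysis & Sample size calculation): 3 arms; block size 8; 95 analysed and 105 recruited per arm, 315 in total; difference of 10 on each outcome; SD 20 for VAS and 16 for HHS; correlation 0.5; final critical value 2.595; 10% allowance for missing data.

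**The plan's own figure.** SD of change = SD × √(2 × (1 − 0.5)) = SD, so 20 for VAS and 16 for HHS. Power = Φ(10/SE − 2.595), with SE = SD × √(1/n₁ + 1/n₂).
- VAS, 95 v 95: SE = 20 × √(2/95) = 2.90; 10/2.90 = 3.45; power = Φ(0.85) = 0.80. The stated 80% is reproduced.
- HHS, 95 v 95: SE = 16 × √(2/95) = 2.32; 10/2.32 = 4.31; power = Φ(1.71) = 0.957, close to the stated 96.2%.

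The sample size is not in dispute.

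**Divisibility.** 8/3 = 2.67, so no block of 8 holds equal numbers of three arms. The nearest split is 3:3:2.

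**Group sizes at 315** (20,000 simulated trials for each of the first two rows):

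| How patients are allocated | Gap, largest minus smallest arm | Exactly equal arms |
|---|---|---|
| Blocks of 8, short arm drawn at random per block | median 6, 95th percentile 12 | about 2% of trials |
| Separate 1-to-3 draw for each patient | median 16, 95th percentile 34 | about 0.3% of trials |
| Blocks of 8, same arm always short | about 39 (118/118/79) | never |

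The last row is 315 × 3/8 = 118.1 and 315 × 2/8 = 78.8.

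**VAS power after 10% loss.**
- Equal arms, 105 × 0.9 = 94.5 each: SE = 2.91; 10/2.91 = 3.44; power = Φ(0.84) = 0.80.
- Blocks of 8, short arm random: mean power over simulated trials about 80.0%, 1st percentile 78.3%.
- Separate draws, illustrated by the median gap of 16 falling between the two arms compared (113 v 97, so 101.7 v 87.3 after loss): SE = 20 × √(1/101.7 + 1/87.3) = 2.92; power = Φ(3.43 − 2.595) = 0.80.
- Same arm always short, short v full (79 × 0.9 = 71.1; 118 × 0.9 = 106.2): SE = 20 × √(1/71.1 + 1/106.2) = 3.06; 10/3.06 = 3.26; power = Φ(0.67) = 0.75.
- Same arm always short, full v full (106.2 each): SE = 2.74; 10/2.74 = 3.64; power = Φ(1.05) = 0.85.

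In the always-short case HHS power is Φ(10/2.45 − 2.595) = Φ(1.48) = 0.93, with SE = 16 × √(1/71.1 + 1/106.2) = 2.45.

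**Sizes that fit.** 315/3 = 105 and 315/9 = 35 are whole numbers of blocks. With blocks of 6, every complete block is balanced and only the last, partial one (3 patients) may not be.

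**The case against.** The strongest reply is that blocks of 8 can still do most of what they are meant to do. The article says the blocks are there to avoid imbalance; it does not promise exact equality. If the short place moves between arms at random, the median gap is 6 patients instead of 16 and the power loss is negligible. If it rotates in order, the arms balance after every three blocks (24 patients). This stands, and it limits the consequence. It does not rescue the text, because neither rule is stated.

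A reader might go further than the article allows in four ways:
- **That the trial will end at 118/118/79 with 75% power.** This needs the same arm to be short in all 39 complete blocks. The article does not describe that, and it would defeat the stated purpose. Even then, if an active arm is short, only its own comparison suffers and the other rises to about 85%. Both comparisons with control fall only if bupivacaine is the short arm.
- **That a block of 8 over three arms amounts to no blocking.** The gaps of 6 and 16 show otherwise.
- **That 315 not being a multiple of 8 is an error.** The total is approximate, and an incomplete last block is routine.
- **That a fixed, published block size lets staff steer allocation.** The injecting surgeon is not among those named as blinded, but the article does not say that the surgeon sees the sequence. Consent and inclusion come about a month before allocation, a nurse obtains the allocation on the day, and post-injection data are collected by a blinded person. Varied, undisclosed block sizes are good practice here, but the prediction risk is secondary.

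**Conclusion.** The point holds as a specification error. A fixed block size of 8 is wrong as written for three arms planned at 1:1:1, and the day-0 procedure contradicts the block scheme. Both follow from the article's text and need no assumption.

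The effect on power does depend on assumptions, because the article does not say how blocks are filled or which procedure is used. With a randomly varying short arm, VAS power stays near 80%. With separate draws, imbalance is larger (median gap about 16) but power changes little at a typical gap. The fall to about 75% is a hypothetical extreme and should be labelled so if quoted. All power figures use the article's own SD, correlation, difference and final critical value, with a uniform 10% loss. This is a low-cost correction, not a major threat to power.

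**What to change.** In Description of methodology, replace the block size of 8 with permuted blocks in a 1:1:1 ratio whose sizes are multiples of 3, preferably varied at random (for example 3, 6 and 9). Keep the sizes out of documents that clinic staff read. Generate one list in advance and keep it concealed. Rewrite the day-0 paragraph so that the nurse obtains the next assignment from that list instead of drawing a fresh number.

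If 8 is a misprint, correct it. If patients have already been allocated by another method, describe what was actually done.

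The cost is a sentence or two in each section and one randomisation list. The sample size and visit schedule do not change.

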### Planned Statistical Analysis & Sample size calculation

A linear regression model for repeated measures will be used to compare the evolution of the scores between the groups. More specifically, a direct likelihood approach will be adopted using an unstructured covariance matrix for the repeated measures (Molenberghs and Kenward, 2007, Section 14.4). The approach has the advantage that less stringent assumptions are made, not only with respect to the covariance structure, but also to the mechanism underlying the missing observations. The approach does not assume that all variances or all covariances will be equal (as is done in classical repeated-measures ANOVA or in a mixed model using only a random subject effect). Furthermore, the approach allows that the missingness depends on the observed values (the so-called missing at random assumption (MAR)), whereas an analysis restricted to patients with complete information assumes the missingness to be completely at random (MCAR) (G. Molenberghs and M.G. Kenward)[45].

The primary analysis is based on intention-to-treat, i.e. all patients who received an infiltration at baseline are included. Appropriate transformations will be considered if needed to meet the statistical assumptions of the regression model. Time point-specific comparisons between the groups of the changes with respect to baseline will be made based on this model. Confidence intervals (CI) of the change as well as the difference (at each timepoint) between groups will be constructed. To protect against an inflated type-I error (due to the presence of two outcomes and two pairwise comparisons), an alpha-level of 0.01 will be used for each comparison with respect to the control group (Bonferroni correction).

A sample size calculation was performed to have at least 80% power to detect in both groups compared with placebo, a clinically meaningful difference in change (baseline-6 months) of 10 mm in VAS and 10 points in HSS. The SD of HSS and VAS is assumed to be equal to 16 and 20 respectively. Estimates are obtained from Frihagen et al. [46] and Qvistgaard [15]. Assuming a moderate correlation of 0.5 between the measurement at baseline and after 6 months, a total of 285 patients are needed, i.e., 95 subjects in each group. With this sample size, 80%power is achieved for VAS and 96.2% for HHS. The number of included subjects will be increased by 10% to compensate for the loss of power due to patients with missing observations (therefore, 105 patients per group will be recruited). Interim analyses are planned after 1/3 and 2/3 of the patients included reach the end of the follow-up period to allow for an early stopping of the study (or accrual of patients in a specific treatment group) due to rejection of the null hypothesis. Using the O'Brien-Fleming method (O'Brien and Fleming 1979) results in respectively |4.495|, |3.178| and |2.595| as critical values for the Z-statistic at the three analysis time points. Otherwise stated, p-values are declared significant if they reach p < 0.000007, p < 0.00148 and p < 0.0095 at the first interim analysis, the second interim analysis and at the final analysis, respectively. (Note that the 'price to pay' for performing the interim analysis is a slightly more conservative alpha-level at the final analysis, i.e. alpha = 0.0095 instead of alpha = 0.01)

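### The primary contrast is a raw change from baseline; a common baseline mean would raise VAS power from about 80% to about 92% with the same patients

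*Protocol article*

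**What the plan says.** All the relevant text is in the protocol article, under Planned Statistical Analysis & Sample size calculation.

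- **Model:** "a direct likelihood approach will be adopted using an unstructured covariance matrix for the repeated measures". No baseline covariate is named, and nothing says that the groups share a baseline mean.
- **Contrast:** "Time point-specific comparisons between the groups of the changes with respect to baseline will be made based on this model".
- **Error rate:** "an alpha-level of 0.01 will be used for each comparison with respect to the control group (Bonferroni correction"). With the two interim looks, the O'Brien-Fleming calculation "results in respectively |4.495|, |3.178| and |2.595| as critical values for the Z-statistic at the three analysis time points".
- **Sizing target:** "at least 80% power to detect in both groups compared with placebo", for "a clinically meaningful difference in change (baseline-6 months) of 10 mm in VAS and 10 points in HSS" (the second score is the Harris Hip Score, HHS).
- **Sizing inputs:** "The SD of HSS and VAS is assumed to be equal to 16 and 20 respectively", and "Assuming a moderate correlation of 0.5 between the measurement at baseline and after 6 months, a total of 285 patients are needed", which is 95 per group. The stated power is 80% for VAS and 96.2% for HHS.

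Table 2 places VAS and HHS on day 0, together with randomisation and infiltration. The Secondary outcomes section confirms that baseline is assessed before any injection. Under Description of methodology, no stratification variables are used.

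**The concern.** If baseline enters the model as one of the repeated measures, each group has its own mean at every visit, and the groups are compared on change, then with complete data the 6-month result is the ordinary change-score comparison. That comparison gives the baseline a weight of exactly 1. The efficient weight is the regression slope of the 6-month score on baseline, which is 0.5 under the plan's own inputs.

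Three things are at stake.

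1. VAS is the limiting endpoint. It sits at the 80% target with nothing to spare.
2. The correlation of 0.5 is an assumption. The SDs are attributed to cited studies; the correlation is not. Change-score power falls quickly if the true correlation is lower.
3. Randomisation is unstratified, so chance baseline differences will occur. The standard error of a VAS baseline difference between two arms is 20 × √(2/95) = 2.90 mm. With a slope of 0.5, a raw-change estimate moves by half of any such difference, so a one-standard-error imbalance shifts it by about 1.5 mm against a 10 mm target.

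**Working it through.** **Inputs, all from the sample size paragraph.** Difference d = 10 on each score; SD 20 (VAS) and 16 (HHS); baseline to 6-month correlation r = 0.5; n = 95 per group; alpha 0.01 per comparison; final critical value 2.595, two-sided. One SD is given per score, so I apply it at both times. Normal approximation throughout.

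**Step 1: reproduce the plan's figure with raw change.**

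- SD of change = SD × √(2(1 − r)). VAS: 20 × √(2 × 0.5) = 20. HHS: 16.
- n per group = 2 × SD² × (z_α/2 + z_β)² / d². VAS at alpha 0.01: 2 × 400 × (2.576 + 0.842)² / 100 = 93.4, so 94. With 2.595 in place of 2.576: 94.5, so 95. The plan states 95.
- Power at n = 95, with √(2/95) = 0.1451. VAS: 10 / (20 × 0.1451) = 3.446, and Φ(3.446 − 2.595) = 80.3%. HHS: 10 / (16 × 0.1451) = 4.308, and Φ(4.308 − 2.595) = 95.7%. The plan states 80% and 96.2%.

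The stated size comes from the raw-change variance.

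**Step 2: the same calculation with baseline adjustment.**

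- Adjusted SD = SD × √(1 − r²). VAS: 20 × √0.75 = 17.32. HHS: 13.86.
- Variance ratio, adjusted to raw: (1 − r²) / (2(1 − r)) = (1 + r)/2 = 0.75.
- Power at n = 95. VAS: 10 / (17.32 × 0.1451) = 3.979, and Φ(3.979 − 2.595) = 91.7%. HHS: z = 4.974, and Φ(4.974 − 2.595) = 99.1%.
- n for 80% VAS power at alpha 0.01: 2 × 300 × (2.576 + 0.842)² / 100 = 70.1, so 71 per group.

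**Step 3: check in the planned type of model.** I took four visits, complete data, all correlations 0.5, VAS SD 20 and 95 per group, and computed the generalised least squares standard error of the 6-month difference.

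| Baseline means | SE (mm) | Effective SD |
|---|---|---|
| Separate by group | 2.902 | 20.0 |
| Common to groups | 2.513 | 17.32 |

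Both rows agree with the closed formulas. The gain therefore comes from the mean structure alone, within the same likelihood approach.

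**Step 4: range over the correlation (VAS, 95 per group, critical value 2.595).**

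| r | Raw change | Common baseline |
|---|---|---|
| 0.3 | 62% | 85% |
| 0.4 | 71% | 88% |
| 0.5 | 80% | 92% |
| 0.6 | 90% | 96% |
| 0.7 | 97% | 99% |

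At r = 0 the adjusted SD is 20 and power is still 80.3%, so the adjusted contrast keeps the planned power for any non-negative correlation.

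**Step 5: both active arms together.** The figures above are for one comparison. The two VAS test statistics share the control arm and so correlate at 0.5. The chance that both exceed 2.595 is about 69% with raw change and 86% with a common baseline. If the aim of detecting the difference in both groups is meant jointly, only the second reaches 80%.

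**The case against.** The strongest objection is that the article never writes down the mean structure. A model with a common baseline mean also yields group differences in change from baseline, so the quoted sentence could stand unaltered under it. Sizing on the larger variance is also compatible with a more efficient analysis. Both points are true as far as they go. But no constraint is stated anywhere, changes from baseline are the stated contrast, and the sizing gives no credit for adjustment. If the constraint is already intended, the remedy is to say so.

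The second objection is that nothing here is invalid: the contrast is unbiased under randomisation, holds its error rate and meets the plan's own 80% target. This stands, and it limits the point to one of efficiency.

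The third is that the size of the gain assumes equal SDs at both times. The VAS entry threshold of 30 mm (Table 1) might narrow the baseline spread. With assumed baseline SDs, a 6-month SD of 20 and r = 0.5, raw-change power would be 87.8% (baseline SD 16) or 90.0% (SD 14), against 91.7% adjusted. So the gain could be smaller than 11 points. Equal SDs are, however, the natural reading of the plan's single SD per score. Writing s₀ and s₁ for the SDs at baseline and 6 months, the raw variance exceeds the adjusted one by (s₀ − r·s₁)², which is never negative. Apart from the negligible cost of estimating the slope, adjustment cannot lose.

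**Conclusion.** The concern holds. As written and as sized, the primary contrast is a raw change from baseline. On the plan's own inputs it carries a variance one third larger than necessary (1/0.75), which costs about 11 points of VAS power (80.3% against 91.7%) and about 3 points of HHS power (95.7% against 99.1%). Put differently, it uses about 94 patients per group where 71 would give the same VAS power.

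The figures rest on r = 0.5, equal SDs at baseline and 6 months, complete data at 95 per group and the normal approximation. The gain shrinks as the correlation rises (97% against 99% at r = 0.7) and grows as it falls (62% against 85% at r = 0.3). It is not a bias or an arithmetic error, but the improvement is free and should be made.

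**What to change.** Keep the direct-likelihood model with unstructured covariance and all four visits, and add one sentence to the analysis section: the baseline mean is constrained to be equal in the three groups (visit effects plus group-by-visit effects at the post-baseline visits only), and the 6-month group difference from this model is the primary estimate for both VAS and HHS.

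Modelling the post-baseline scores with baseline-by-visit as a covariate gives nearly the same answer. The constrained version fits this plan better, because it keeps patients with a missing baseline and directly supplies the confidence intervals for change that the plan promises.

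If this constraint is already intended, state it. Either way, fix it before the first interim analysis, since stopping decisions rest on this contrast. The data, software, missing-at-random basis and estimand under randomisation do not change, and no extra patients are needed. The sample size can stay at 95 per group before the dropout allowance, with the surplus as protection against a correlation below 0.5.

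### Single-step Bonferroni over the four primary tests is valid but gives up power; Holm step-down keeps the same 0.04 bound and, if all four planned effects are real, lifts VAS power from about 80.5% to about 89.5%

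*Protocol article*

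**What the plan says.** All of this stands in the protocol article, section *Planned Statistical Analysis & Sample size calculation*.

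- The adjustment is made "due to the presence of two outcomes and two pairwise comparisons", which gives 2 x 2 = 4 primary tests.
- The method is fixed: "an alpha-level of 0.01 will be used for each comparison with respect to the control group (Bonferroni correction"). No step-down order, hierarchy or reuse of level is mentioned.
- The sequential boundaries are built on that 0.01. O'Brien-Fleming gives "4.495|, |3.178| and |2.595| as critical values for the Z-statistic at the three analysis time points", and the final look is at "alpha = 0.0095 instead of alpha = 0.01".
- The design targets are "a clinically meaningful difference in change (baseline-6 months) of 10 mm in VAS and 10 points in HSS".
- The power differs between the outcomes: "With this sample size, 80%power is achieved for VAS and 96.2% for HHS".

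**The concern.** Under single-step Bonferroni each test stays at 0.01 whatever the other three show. By the plan's own figures the HHS tests are much stronger than the VAS tests, and VAS sets the sample size. When the HHS tests are rejected, the level spent on them is not passed on to VAS.

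Holm's procedure passes it on. It controls the family-wise error under any dependence between the tests, so it needs no correlation that the protocol does not give. It can never reject fewer hypotheses than Bonferroni. What is at stake is power on the limiting outcome, not validity.

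**Working it through.** **Inputs from the protocol.** Difference 10 mm (VAS) and 10 points (HHS). "The SD of HSS and VAS is assumed to be equal to 16 and 20 respectively". "Assuming a moderate correlation of 0.5 between the measurement at baseline and after 6 months". 95 evaluable patients per group, two-sided tests at 0.01, looks at 1/3, 2/3 and the end.

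**Inputs assumed.** The VAS-HHS correlation is not given, so it was varied from 0 to 0.9 for a fixed sample and from 0 to 0.7 with three looks. The two comparisons share the control group, so their statistics correlate at 0.5.

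**Step 1: reproduce the plan.** SD of change = SD x sqrt(2(1 - 0.5)) = SD, that is 20 and 16.

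- VAS: 10 / (20 x sqrt(2/95)) = 3.446. Power at 0.01 = Phi(3.446 - 2.576) = 80.8%, or 80.3% at 0.0095. The stated 80% is reproduced.
- HHS: 10 / (16 x sqrt(2/95)) = 4.308. Power at 0.01 = Phi(4.308 - 2.576) = 95.8%, against the stated 96.2%. The small gap does not affect the point.
- Boundaries: 2.595 x sqrt(3) = 4.495 and 2.595 x sqrt(1.5) = 3.178, as stated.

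So the stated 80% is the single-step Bonferroni power of one VAS comparison.

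**Step 2: where the gain comes from.** Holm at total 0.04 tests the ordered statistics at 0.04/4 = 0.01, 0.04/3 = 0.0133, 0.04/2 = 0.02 and 0.04. Fixed-sample power of one VAS test at each level:

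| Level | VAS power |
|---|---|
| 0.01 | 80.8% |
| 0.0133 | 83.4% |
| 0.02 (both HHS tests rejected) | 86.9% |
| 0.04 (the other VAS test rejected too) | 91.8% |

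The HHS rejections alone bring VAS to about 87%. The rest needs the other product's VAS test to be rejected as well.

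**Step 3: simulation.** 200,000 trials, three looks, 95 per group, all four effects as planned, no arm closed early. A test counts as rejected if it crosses the boundary for its Holm level at any look.

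| Power | Bonferroni | Holm |
|---|---|---|
| VAS, one product | about 80.5% | about 89.5% |
| VAS, both products | about 69% | about 84% |
| All four tests | 65-68% | 83-84% |

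The first two rows hardly change with the VAS-HHS correlation. The last is for correlations of 0.3 to 0.7.

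**Step 4: less favourable scenarios, same three looks.**

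- Only one product works: VAS 80.5% to 83.0%.
- VAS effects real, HHS effect absent in both products: VAS 80.5% to 82.3%.

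**Step 5: error.** Under the global null the two procedures have the same family-wise error, 3.3% to 3.8% across the correlations tried. With VAS null and HHS effective it is about 1.9% for Bonferroni and about 3.5% for Holm. Both stay below 0.04.

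**Step 6: other starting level.** If the family level were 0.05, so 0.0125 per test, VAS power with three looks would be about 82.5% under Bonferroni and about 91% under Holm. The point does not depend on that choice.

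**The case against.** **Nothing is wrong as written.** Bonferroni is a valid, prespecified choice. The sample size and boundaries follow from it, and the power target is met per comparison. This stands in full: the point is a cheap improvement, not a correction of an error. A reader might infer that the family-wise error is not controlled, and the document does not support that. A reader might also infer that the plan misses its own 80% target, because power for both products on VAS is about 69% and the target speaks of both groups. But the stated 80% reproduces as the power of a single comparison, so the document does not show that a joint target was meant.

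**The 9-point gain is the favourable case.** It needs all four effects at full planned size. The article itself says in *Background* that the effect of hyaluronic acid in the hip is unresolved, and in *Corticosteroids* that the steroid effect lasts only some months. This stands, and the gain must be quoted with its scenario.

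**Early closure.** The plan allows the study, or accrual to one group, to stop on rejection, without saying which rejection triggers this. One HHS test has about a 63% chance of having crossed by the second look if its effect is as planned. If a product's data ended at its first rejection, VAS power would be about 53% under Bonferroni and roughly 64% to 71% under Holm, depending on the VAS-HHS correlation. Holm still helps, but the figures of 80.5% and 89.5% do not describe that trial.

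**Confidence intervals.** The plan promises intervals for the group differences. Under Holm a difference can be declared significant while its Bonferroni-level interval includes zero. This is a real cost.

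**Conclusion.** The point holds as an efficiency gain. With the family-wise bound kept at 0.04, Holm raises VAS power per product from about 80.5% to about 89.5%, and power for both products on VAS from about 69% to 84%. This rests on the plan's SDs and correlation, 95 evaluable patients per group, all four effects real, and follow-up of VAS continuing after an HHS crossing. With one product effective, or no HHS effect, the gain shrinks to about 2 to 2.5 points, but it is never negative.

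Two stronger statements are tempting and should not be made. The gain is not due to HHS alone: those rejections take VAS to about 87%, and the other VAS rejection supplies the rest. Nor is it free of any extra error: the guaranteed bound is the same, but with VAS null and HHS effective the actual error rises from about 1.9% to about 3.5%.

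**What to change.** Before any interim data are seen, replace Bonferroni with Holm over the four primary hypotheses. Order the four statistics, compare the largest with the first boundary, and move to the next only after a rejection. At look k each boundary is its final constant times sqrt(3/k):

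| Step | Level | Look 1 | Look 2 | Final | Final constant if starting level is 0.0125 |
|---|---|---|---|---|---|
| 1 | 0.01 | 4.495 | 3.178 | 2.595 | 2.519 |
| 2 | 0.0133 | 4.325 | 3.058 | 2.497 | 2.419 |
| 3 | 0.02 | 4.077 | 2.883 | 2.354 | 2.272 |
| 4 | 0.04 | 3.625 | 2.563 | 2.093 | 2.004 |

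Step 1 is the boundary already in the plan. State as well that the confidence intervals stay at the Bonferroni level and may not match a step-down decision, and say how testing of the remaining hypotheses continues after a partial rejection at an interim look.

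The cost is a short piece of analysis text, three further sets of boundaries and a few lines of code. Patient numbers and visits do not change.
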